#### Participant timeline {13}

All consecutive trauma patients admitted directly from the injury scene who require RBC transfusion with a risk of massive transfusion are screened on admission. Eligible patients are then rapidly enrolled by the study investigator. They should be randomized and treated accordingly within 60 min post-admission. After patient treatment, follow-up includes hourly visits until 6 h post-admission, as well as visits at 12 and 24 h to measure prothrombin ratio, assess hemorrhage control and monitor adverse events. Thrombo-embolic events are under special scrutiny during the entire hospital stay because they are frequently expected adverse effects of PCC treatment. Each suspicious thrombo-embolic event should be confirmed with venous Doppler echography or angiography and treated following standard practice. Thromboprophylaxis is left to physician discretion. Patients are followed for 28 days with the last visit aiming at collecting the Glasgow outcome scale extended (GOSE) for patients with brain lesions on initial cerebral imaging, mortality, and place of living (Fig. 1).

**Fig. 1 Fig1:**
[figure not shown]
Design of the study

#### Sample size {14}

Total blood consumption was estimated in the control group based on 1-year consumption in Grenoble University Hospital and Annecy General Hospital; we found that patients with our eligibility criteria received 12 units on average of RBC, FFP, and platelets. We consider a reduction of 3 units as clinically significant since 3 units represent 1 L of blood products. Thus, a 25% decrease in transfused blood products in the first 24 h is expected (from an average of 12 transfused units in the control group to 9 transfused units in the experimental group). The study needs to include 162 patients per group to demonstrate this 25% reduction with 80% power and α-risk of 0.05, bilateral test (nQuery, Sample Size and Power Calculation, “Statsols”, Statistical Solutions Ltd., Cork, Ireland, blood product units transfused do not follow a normal distribution). To compensate for the estimated lost-to-follow-up, the trial plans to include 350 patients.

#### Recruitment {15}

All centers are level-I trauma centers in France with sufficient recruitment of severe trauma patients. Before the start of the study, a feasibility questionnaire has circulated between all centers and they were asked for potential inclusions in the study. They all agreed to include between one and two patients each month. Regular newsletters will be sent and all participating centers are part of a national network for trauma care (GITE group).

### Assignment of interventions: allocation

#### Sequence generation {16a}

Randomization will be performed by sealed envelopes available at the investigator site. Randomization will be by block of random size from 2 to 6, stratified by center. The randomization list will be created and maintained by the study sponsor. Randomization envelopes to be opened will be created prior to the study by the coordinating pharmacy and made available during the site visit. The integrity and presence of the envelopes will be checked at each monitoring visit.

#### Concealment mechanism {16b}

Allocation sequence is implemented through sequentially numbered, opaque, sealed, envelopes. Envelopes have been created by the coordinating pharmacy in Grenoble and provided to each investigating site pharmacy which manages the stock. Site pharmacy provides 4 sequentially numbered envelopes to the investigating team and renew the stock after each randomization. Envelopes are sealed with inviolable tapes making any opening visible. Therefore, the investigating team cannot modify the inclusion decision after allocation without such a modification being noticed by the hospital pharmacy and monitoring team.

#### Implementation {16c}

An independent statistician will generate the allocation sequence, a clinician investigator (clinician trained in trauma resuscitation) will enroll participants; an unblinded, trained nurse not involved in patient care assign participants to one of the study arms by unsealing randomization envelope.

### Assignment of interventions: blinding

#### Who will be blinded {17a}

After enrolment, the blinded clinician investigator conveys to the unblinded, dedicated, trained nurse patient’s name, weight, and study number. This nurse does not participate in the resuscitation of the patient. The nurse prepares the solution to be administered (placebo (saline solution 0.9%) or PCC (1 ml/kg) according to the assignment specified in the randomization envelope. Treatment is stored in a designated and closed refrigerator and administered in opaque syringes by the same dedicated nurse at a speed of 120 mL/h with syringe pumps.

The investigating team and the patient are blinded (clinician investigator and any MD implied in patient care, nurses, site clinical research assistants). The only unblinded person in the entire process is the dedicated nurse unsealing the envelope and preparing the study drug or placebo to be administered.

Several means are deployed to ensure masking: the dedicated nurse is not involved in the care of the included patient as verified by the monitoring team on every visit. Perfusion material (syringes, filling pipes, and dressings) is opaque, drug storage, randomization, and study drug preparation performed in dedicated protected areas.

The site pharmacy and pharmacy site monitor are not blinded. Statisticians and data monitors are blinded to treatment allocation.

#### Procedure for unblinding if needed {17b}

Unblinding is possible if the information of the allocated treatment is necessary for the care of the included patient. The clinician investigator will retrieve this information from the on-site pharmacist.

To retrieve the information, the referring person will complete on a standard form:
The contact details of the physician, clinician investigator or not, or the pharmacist who called (name, first name, qualification of the caller, address, telephone number).The name of the study.The date of the call, the description of the clinical event motivating the call: type of event, start date, and treatment modalities.If the event is classified as a serious adverse event.The action following this call: unblinding, action to be taken to explore the effect and allow diagnosis, treatment of the effect.

The randomization list is stored in the clinical pharmacy of each participating center. This information will be sent as soon as possible to the study sponsor by e-mail.

The monitoring unit will be systematically unblinded in case of a suspected unexpected serious adverse reaction before reporting to the competent authorities and possibly annually when the annual safety reports are redacted.

### Data collection and management

#### Plans for assessment and collection of outcomes {18a}

An electronic case report form (eCRF, CSonline by clinsight) will be composed for the study. The persons responsible for completing the eCRF will be clearly identified in the task delegation document.

Grenoble University Hospital is the sponsor of the study and is responsible for study oversight and quality controls. Data are collected by the investigating centers’ staff on the electronic case report form. Pseudo-anonymized data are stored by and belong to the sponsor. Participating centers are monitored by a dedicated department, independent of the scientific team and investigators who designed the project. Centers are visited regularly to control patient data, ethical standards, patient safety, respect of masking protocol, and investigational product handling and storage. The primary endpoint is monitored in all patients.

All visits will be the subject of a monitoring report in writing. A copy will be sent to the Principal Investigator.

#### Plans to promote participant retention and complete follow-up {18b}

The primary outcome is collected at day 1 (total blood consumption). This endpoint is easily verified through blood bank data. Patient follow-up will be performed until day 28. Considering the clinical acuity of the patients and their admission to the ICU, no specific action is planned to promote participant retention.

#### Data management {19}

Data management will follow Grenoble-Alpes university hospital procedures (data validation, basic freezing, backup, data reviews before unblinding). A data entry dictionary will be made available to investigators and their teams and traceability of requests for corrections and corrections made on the eCRF.

#### Confidentiality {27}

In accordance with the law (Articles L.1121-3 and R.5121-13 of the Public Health Code), persons with direct access to data will take all necessary precautions to ensure the confidentiality of information relating to experimental drugs, research, and the persons involved, particularly with regard to their identity and the results obtained. These persons, in the same way as the investigators themselves, are subject to professional confidentiality.

During or at the end of the interventional research, all patient data collected and transmitted to the sponsor by the investigators will be pseudo-anonymized. Under no circumstances should the names or addresses of the patients be exposed. Only the first letter of the subject’s surname and first name will be recorded, accompanied by a coded number specific to the research, indicating the order of inclusion of the subjects.

The promoter will ensure each participant’s approval through written informed consent and assure access to their individual data and that no personal data are retained except for the bare minimum required for quality control.

#### Plans for collection, laboratory evaluation, and storage of biological specimens for genetic or molecular analysis in this trial/future use {33}

This is not applicable.

### Statistical methods

#### Statistical methods for primary and secondary outcomes {20a}

The risk of alpha error corresponds to a usual threshold: 5%. All our tests will be bilateral. The initial characteristics of the patients will be represented in a comparative table according to the two treatment groups. Quantitative and qualitative variables will be presented with the usual parameters, mean, and standard deviation as well as numbers and percentages.

##### Analysis of the main outcome

The main outcome is the total blood consumption (RBC, FFP, and platelets). It will be analyzed after verification that the time spent in the study up to H24 is not significantly different between the two groups. If this duration is not different, the total number of units transfused over 24 h between the two groups will be compared using a bilateral student intent to treat *t* test (if the application conditions are not met, we will use a non-parametric Mann-Whitney *U* test). If the duration is different, the amount of blood products used per hour between the two groups will be compared using an intention-to-treat Student *t* test (= total number of bags transfused over 24 h divided by the time spent in research during the first 24 h), in order to control for an attrition bias created by patients who died before 24 h.

The per-protocol analysis will be performed on patients who actually received treatment within 1 h of admission to the hospital.

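### A significance test on time in study can switch the primary variable to units per hour, a ratio dominated by early deaths, so the primary result becomes unreliable when early mortality differs between arms

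*Protocol article*

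**What the plan says.** The Outcomes section {12} defines the primary outcome as a count: red cell, plasma and platelet units over the first 24 hours after admission. The Sample size section {14} is built on that count, "from an average of 12 transfused units in the control group to 9 transfused units in the experimental group", "with 80% power and α-risk of 0.05, bilateral test", and adds that "blood product units transfused do not follow a normal distribution".

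The section Analysis of the main outcome makes the analysis conditional: "It will be analyzed after verification that the time spent in the study up to H24 is not significantly different between the two groups". The gate test is not named.

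- If the gate is not significant, total units are compared by t test, or by Mann-Whitney if the t test's conditions fail.
- If it is significant, the variable becomes "total number of bags transfused over 24 h divided by the time spent in research during the first 24 h", compared by Student t test. No non-parametric alternative is given for this branch.

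The stated purpose is to control attrition bias from deaths within the first day. The secondary analysis applies the same strategy to each blood product separately.

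**The concern.** Time in study up to 24 hours is a post-randomisation outcome that mostly reflects survival. The rule lets it decide which variable carries the primary hypothesis. Total units and units per hour answer different questions, and only the first has a target difference and a sample size behind it.

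The ratio would be a fair correction only if transfusion ran at a steady rate. The protocol's own definition of massive transfusion sets 3 red cell units in the first hour beside 10 in 24 hours, that is 3 per hour against 10/24 = 0.42 per hour. Need is therefore front-loaded, and a short denominator inflates the rate. The Outcomes section explains that mortality after trauma depends on more than haemorrhage, as part of the case for measuring blood use. The per-hour branch brings mortality back into the primary test. At stake is whether the primary conclusion concerns blood use when survival differs between arms, which is the situation the rule was written for.

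**Working it through.** **Inputs from the protocol.** Means of 12 and 9 units, two-sided 5%, 80% power, 162 per group.

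**Inputs not in the protocol, assumed.** SD, 24-hour mortality (5–20%), timing of deaths (mean 5–10 h), shape of transfusion over time (front-loaded, time constant 4 h), and non-survivors' need (1.0 or 1.5 times that of survivors).

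**1. The plan's own figure.** No SD is printed, so 162 can only be inverted: SD = 3 × √(162/2) / (1.960 + 0.842) = 27/2.802 = 9.6 for a t test. Allowing for a rank test gives about 9.0 to 9.4. The sample size is not in dispute, and 9.6 is used below.

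**2. What the ratio measures.** Twelve units over 24 h is 12/24 = 0.5 per hour. Twelve units with death at 2 h is 12/2 = 6 per hour, twelve times higher for the same blood use. In the simulations, patients dying early averaged 1.5–2.9 per hour, survivors 0.5, and the early deaths supplied 60–86% of the variance of the ratio.

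A 10-point difference in early deaths therefore moves the mean ratio by 0.10 × (1.5 − 0.5) = 0.10 to 0.10 × (2.9 − 0.5) = 0.24 per hour. The full target effect in 24-hour survivors moves it by 12/24 − 9/24 = 0.125 per hour. The two shifts are of similar size and can cancel or add.

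**3. How often the gate fires.** Nearly all survivors have the same time in study, so the gate behaves much like a test of the proportion dying early. With 162 per arm, z = difference / √(2p̄(1 − p̄)/162) and power ≈ Φ(z − 1.96):

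- 10% v 15%: 0.05/0.0367 = 1.36, power 27% (simulated 26%)
- 5% v 10%: 0.05/0.0293 = 1.71, power 40% (simulated 40%)
- 10% v 20%: 0.10/0.0397 = 2.52, power 71% (simulated 70%)
- 5% v 15%: 0.10/0.0333 = 3.00, power 85% (simulated about 87%)

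**4. The whole rule.** Simulated with 162 per arm, skewed units with mean 12 and SD 9.6, and a rank test as gate. Ranges cover the assumed death timing and severity and, for totals, t test or Mann-Whitney.

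| Early deaths | True units | Gate fires | Planned rule rejects | Totals only reject |
|---|---|---|---|---|
| equal, 5–15% | no effect | 4–6% | 5–7% | 5–6% |
| 10% v 5% | no effect | 40% | 11–17% | 5–6% |
| 20% v 10% | no effect | 70% | 35% | 5% |
| 15% v 5% | no effect | 86–87% | 26–49% | 5–9% |
| equal, 10% | 12 v 9 | 5% | 78–87% | 78–88% |
| PCC 15%, placebo 5% | 12 v 9 | 87% | 14–21% | 84–95% |
| PCC 5%, placebo 15% | 12 v 9 | 87% | 96% | 73–84% |

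In the last two rows the reduction in need is identical; only the direction of the mortality difference changes.

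**5. Calibration.** The upper power of 88% exceeds the design's 80%. That is what one expects if the SD falls with the mean: 9.6 × 9/12 = 7.2, and 3/√((9.6² + 7.2²)/162) = 3.18, giving Φ(3.18 − 1.96) = 89%. The contrast between rules matters here, not the absolute power.

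**The case against.** The strongest defence is that the rule is prespecified, has a sound motive and seldom acts. With equal early mortality this stands: the switch is rare, type I error barely moves and power is close to that of the ungated test. A reader might infer that the trial as a whole tests mortality instead of blood use. The protocol does not support that; it is true only of the per-hour branch, and it matters only when early mortality differs.

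A reader might also infer that the gate will usually miss a mortality difference. That holds for modest differences such as 10% versus 15%, but not for 5% versus 15%. Since the gate test is unnamed, every such figure assumes one.

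The missing non-parametric alternative may be a product of condensing the protocol into an article. Even with Mann-Whitney on the ratio, no effect on need and 15% versus 5% deaths gave about 13–25% rejection in simulation. The distortion shrinks but remains.

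Two further readings carry little weight. Counting units from admission while dividing by time in research may put two clocks in the ratio, but treatment is due within an hour of admission, so the offset is at most about 1/24 = 4% for a 24-hour survivor and applies to both arms. The choice between t test and Mann-Whitney on totals is named in advance and left type I error near 5%.

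The last objection stands in full: totals without a gate are themselves lowered by early death and so favour the arm with more of it. The remedy must say so.

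**Conclusion.** The point holds in a limited form. The protocol itself fixes a rule under which a significance test on a post-randomisation outcome replaces the defined and powered primary variable with a ratio dominated by early deaths. A separate analysis plan might refine this, but the defect is in what is stated, not in missing detail.

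Where early mortality is equal, the consequence is slight. Where it differs materially, the rule can produce a significant primary result with no effect on transfusion need, or hide a real 3-unit reduction. The arithmetic on the ratio depends on no assumption about mortality. The rejection rates do depend on the assumed SD, mortality, death timing and front-loading, and should be read as ranges. Because this is the primary analysis and the conclusion can reverse by branch, it should be corrected before unblinding.

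**What to change.** - Delete the gate. State one primary analysis: total units in the first 24 hours in all randomised patients, whatever their survival time, by one test named before unblinding. The mean difference with a robust standard error is one option and matches the 3-unit target.
- Prespecify an analysis that ranks deaths before 24 hours as the worst outcome, and report it beside the primary result and 24-hour mortality, which is already a secondary outcome.
- Keep units per hour at most as a sensitivity analysis.
- Apply the same to red cells, plasma and platelets.

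This costs wording only; no new data are needed. The price in interpretation should be written into the plan: ungated totals fall when patients die early, so fewer units cannot be read as benefit unless the death-ranked analysis and 24-hour mortality agree.

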The investigators acknowledge that total blood transfusion is only a surrogate marker of the severity of the bleeding. However, the AVERT Shock trial successfully applied this endpoint based on the rationale that reduction of blood transfusion is an objective of innovative trauma resuscitation [20]. The amount of transfusion has been shown to correlate with severe complications and poor clinical outcomes [10, 21, 27]. Specifically, Moore et al. noted that transfusion of packed red blood cells was the strongest predictor for the development of multi-organ failure (odds ratio = 8.6) [11]. The strategy tested in the present trial hence carries the potential to reduce morbidity, mirrored by the length of stay in ICU and the duration of mechanical ventilation, by reducing the amount of used blood products. The investigators are aware that despite existing guidelines, hemorrhage management may vary. This aspect is acknowledged by the center-based stratification of the randomization process.

Considering the fact that PCC use remains a matter of debate after severe trauma because of an associated potential high thromboembolic risk in this specific patient group; indeed, the use of PCC has repeatedly been shown to result in an excessive overshoot of thrombin generation in both in vitro studies [28, 29] and clinical studies including trauma patients [30]. PROCOAG Trial provides the advantage to explore the safety of empiric PCC administration based on the high clinical probability of active hemorrhage and massive transfusion.

As a pragmatic study, this trial aims at testing the effect of PCC administration in combination with standard care in a *real-life* context. With a high level of proof and quality standard, a positive result might already affect the management of severe trauma patients at risk of massive transfusion as this study investigates PCC efficacy, safety, and cost in this indication.

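### Randomisation is stratified by centre but the primary test ignores centre, so if centres differ the test is conservative and forgoes some power

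*Protocol article*

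**What the plan says.** Under Sequence generation {16a} the protocol states: "Randomization will be by block of random size from 2 to 6, stratified by center". Study setting {9} gives twelve hospitals. The Discussion concedes that the care of bleeding patients can differ even where guidelines exist, and adds: "This aspect is acknowledged by the center-based stratification of the randomization process".

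The analysis sections do not use centre. For the primary outcome, "the total number of units transfused over 24 h between the two groups will be compared using a bilateral student intent to treat" t test; a Mann-Whitney U test replaces it if the conditions for the t test fail. If time in study differs between the arms, a t test on units per hour is used instead. The separate RBC, FFP and platelet quantities follow the same strategy. Thromboembolic events and location at day 28 get a chi-square or Fisher test, and mortality a Kaplan-Meier comparison. The only multivariable work named concerns censoring in the cost analysis. The sections on additional analyses and on non-adherence add no centre term.

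**The concern.** Blocking within centre makes the arms nearly equal in size at every hospital, so differences between hospitals largely cancel out of the treatment difference. A two-sample test that ignores centre still counts those differences as noise. Its standard error then describes a trial randomised without strata, not this one. The design has paid for precision that the analysis does not collect.

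A centre effect is plausible here because the outcome counts what the local team chooses to give. The standard-care section allows an RBC:FFP ratio anywhere from 1:1 to 2:1. As an illustration, a patient given 6 RBC receives 6 + 3 = 9 units at one end of that range and 6 + 6 = 12 at the other, before platelets. That spread equals the target effect. It shows that practice can move the outcome, but it does not measure how far centres actually differ.

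At stake are some power and a significance level that differs from the declared one. This is a named choice of test, not a detail left for an analysis plan.

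**Working it through.** **Inputs from the protocol.** Effect: "from an average of 12 transfused units in the control group to 9 transfused units in the experimental group", a difference of 3 units. Sample size: "The study needs to include 162 patients per group to demonstrate this 25% reduction with 80% power and α-risk of 0.05, bilateral test". Analysis level: "The risk of alpha error corresponds to a usual threshold: 5%. All our tests will be bilateral". Twelve centres, so 324/12 = 27 patients each on average.

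**Inputs not given.** The SD is not stated; the protocol reports only that "patients with our eligibility criteria received 12 units on average of RBC, FFP, and platelets". The ICC is not stated either, so it is varied from 0 to 0.20 as an assumption.

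**The plan's own figure.** Without an SD, 162 cannot be reproduced independently. Solving the two-mean formula backwards for a t test gives

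SD = 3 × √(162/2) / (1.960 + 0.842) = 27 / 2.802 ≈ 9.64 units.

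With that SD the formula returns 162 per group and 80.0% power. If the calculation was for a Mann-Whitney test (relative efficiency 0.864 to 0.955), the implied SD is about 9.0 to 9.4.

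**Effect of ignoring centre.** Hold the total SD at 9.64 and take allocation as balanced within centre. The true variance of the difference is (1−ICC) × 2SD²/n, but the unadjusted t test uses 2SD²/n. Write w = √(1−ICC); the ratio of the effect to the unadjusted standard error is 2.802.

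- Standard error too large by 1/w
- True two-sided level of the unadjusted test: 2[1 − Φ(1.960/w)]
- Power, unadjusted: Φ((2.802 − 1.960)/w)
- Power, centre in the model: Φ(2.802/w − 1.960)
- n per group for 80% if adjusted: 162 × (1−ICC), rounded up

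At ICC 0.10, w = 0.949. The true level is 2[1 − Φ(2.066)] = 0.039, unadjusted power is Φ(0.887) = 81.3%, and adjusted power is Φ(0.993) = 84.0%.

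| Assumed ICC | SE ratio | True level, unadjusted | Power, unadjusted | Power, adjusted | Gain (points) | n/group, adjusted |
|---|---|---|---|---|---|---|
| 0 | 1.00 | 0.050 | 80.0% | 80.0% | 0 | 162 |
| 0.02 | 1.01 | 0.048 | 80.2% | 80.8% | 0.6 | 159 |
| 0.05 | 1.03 | 0.044 | 80.6% | 82.0% | 1.4 | 154 |
| 0.10 | 1.05 | 0.039 | 81.3% | 84.0% | 2.7 | 146 |
| 0.20 | 1.12 | 0.028 | 82.7% | 88.0% | 5.3 | 130 |

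**Simulation with normal outcomes.** 12 centres, 324 patients, blocks of 2, 4 or 6 within centre, 4,000 runs per cell. Monte Carlo error is about 0.3 points for the level (√(0.05 × 0.95/4000)) and 0.6 for power (√(0.8 × 0.2/4000)). Entries are t test / Mann-Whitney / centre-adjusted linear model.

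| Assumed ICC | Type I error | Power |
|---|---|---|
| 0 | 0.0475 / 0.0485 / 0.0472 | 0.7850 / 0.7645 / 0.7827 |
| 0.05 | 0.0495 / 0.0512 / 0.0532 | 0.8062 / 0.7842 / 0.8178 |
| 0.10 | 0.0392 / 0.0370 / 0.0482 | 0.8128 / 0.7982 / 0.8350 |
| 0.20 | 0.0300 / 0.0320 / 0.0505 | 0.8185 / 0.7965 / 0.8745 |

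At ICC 0.05 the loss of level cannot be told from noise; at 0.10 and 0.20 it is clear.

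**Simulations with skewed counts** (12 × 27 patients, SD about 9.5). In one set, t test against centre-adjusted analysis gave 82.7% and 85.3% at ICC 0.10 (gain 2.6) and 83.1% and 87.3% at 0.20 (gain 4.2). Mann-Whitney against van Elteren gave 77.5% and 79.5% (gain 2.0), then 78.7% and 83.5% (gain 4.8). A second set, with negative-binomial counts and 3,000 runs, gave for the rank pair 82.4% and 81.2% at ICC 0, 84.5% and 84.7% at 0.05, 85.1% and 86.3% at 0.10, and 89.1% and 92.7% at 0.20. The gains are −1.2, 0.2, 1.2 and 3.6 points. Power levels depend on the assumed shape of the counts; the gains are the comparable part.

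**The case against.** A reader might infer that the trial is underpowered. The documents do not support that. The 162 per group was set for 80% power with no centre adjustment stated, and in the formula the unadjusted t test stays between 80.0% and 82.7% at the implied SD. What is forgone is a gain above target. Where the Mann-Whitney test sits below 80% in some runs, the cause is that test at that SD and shape, since its power does not fall as the ICC rises.

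Nor do the documents support a reading that the result would be biased or too readily positive. The error is conservative and the estimate stays unbiased.

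The size of the effect is also unsupported by any figure in the protocol. All sites are level-I centres working to the same European guidance, so the ICC could be small, and up to 0.05 the gain is about a point or nothing. Because the protocol expects non-normal counts, the rank route may well apply; there the gain at 0.10 was only 1.2 to 2.0 points, and at ICC 0 the stratified test may cost about a point. This stands as a limit on size, not on direction.

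Two further points stand. The Discussion says only that stratification acknowledges variable management; it does not claim that the problem is solved. And no confidence interval is specified for the primary difference, since the one planned interval is for mean cost, so a complaint about a stated interval has no text behind it.

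**Conclusion.** The mismatch is real: centre is used to randomise and then dropped from the named primary test. To the extent that centre explains outcome variance, the standard error is too large by about 1/√(1−ICC), the test runs below 5%, and power is forgone. On the mean-based route that is about 0 to 1.5 points at an ICC up to 0.05, 2 to 3 at 0.10 and 4 to 6 at 0.20; the rank route falls at or somewhat below these figures. The direction is secure. The size rests on an assumed ICC, a back-solved SD and near-balance within centre.

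This is a recommendation on efficiency and on coherence between design and analysis. It does not threaten the validity of the trial. For binary and time-to-event outcomes no size was computed, so a reader should not infer that every secondary analysis must be stratified across twelve small strata.

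**What to change.** Amend Analysis of the main outcome so that centre enters as a fixed or random effect in the primary comparison, including the units-per-hour version, and do the same for the RBC, FFP and platelet quantities. If the rank route is taken, replace the Mann-Whitney test with the van Elteren test. State in advance how very small centres are pooled. For binary and time-to-event secondary outcomes, use centre-stratified methods only where event numbers allow.

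The cost is wording, settled before unblinding. Because the unstratified tests are written into the protocol, the change may need an amendment under the article's amendment section as well as an entry in the SAP. No patients or data are added, since centre is known for everyone. If centre has no effect the loss is negligible: 0.2 points for the linear model in the normal simulation (78.50% to 78.27%) and about one point for the rank test.
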